#### Exclusion criteria

2.4.2

Any absolute or relative contraindication to exercise testing or training according to international guidelines; History of a major cardiovascular event (e.g., acute myocardial infarction, unstable angina) or cardiovascular procedures (e.g., percutaneous coronary intervention, coronary artery bypass grafting) within the 2 months preceding enrollment; Implantation of a fixed-rate pacemaker where the upper heart rate limit is programmed below the target heart rate calculated for physical training; Specific contraindications to blood flow restriction therapy, including a documented history of deep vein thrombosis (DVT), peripheral vascular disease, active thrombophlebitis, or severe peripheral neuropathy; Inability to perform resistance training due to severe orthopedic or cognitive limitations.

### Primary and secondary outcomes

2.5

#### Primary outcome

2.5.1

The primary outcome of this trial will be the longitudinal change in serum N-terminal pro-brain natriuretic peptide (NT-proBNP) levels from baseline to the completion of the 16-week intervention. Serum NT-proBNP is a gold-standard, objectively measured biomarker reflecting myocardial wall stress and hemodynamic overload. Reductions in its concentration serve as a surrogate marker for positive cardiac reverse remodeling and are strongly correlated with reduced long-term cardiovascular mortality and hospitalization rates in individuals with heart failure.

#### Secondary outcomes

2.5.2

To capture a comprehensive clinical profile of the chronic adaptations induced by the training protocols, the following secondary outcomes will be evaluated at baseline and after 16 weeks:

Health-Related Quality of life: Assessed using the Minnesota Living with Heart Failure Questionnaire. This specific instrument evaluates the patients' perceptions of how the disease affects their physical, socioeconomic, and emotional dimensions, acting as a powerful clinical predictor of disease stability and patient independence.

Functional Capacity and Exercise Tolerance: Measured via the distance covered in the 6-Minute Walk Test. Functional capacity is an independent predictor of all-cause mortality in heart failure, and its improvement directly relates to real-world functional independence.

Peripheral Muscular Strength: Evaluated through the submaximal one-repetition maximum 1RM prediction protocol. Skeletal muscle wasting and weakness are core features of the pathophysiological progression of heart failure; enhancements in peripheral muscular strength are strongly linked to improved mechanical efficiency and reduced clinical frailty.

Echocardiographic Ventricular Function: Left and right ventricular structural and functional remodeling will be assessed via resting transthoracic echocardiography. Key parameters include left ventricular ejection fraction (LVEF), tricuspid annular plane systolic excursion (TAPSE), and diastolic filling pressures (*E/e'* ratio) to document central cardiac adaptations.

Clinical Safety and Adverse Events: The occurrence of any relative or absolute adverse event (e.g., symptomatic hypotension, persistent muscular pain, dizziness, or pre-syncope), all-cause hospitalizations, or clinical worsening of the heart failure condition will be systematically recorded throughout the 16-week cycle to establish safety parameters.

#### Randomization and allocation concealment

2.5.3

Following the completion of baseline assessments, participants will be randomly assigned (1:1) to either the Conventional Resistance Training (CRT) group or the Blood Flow Restriction Resistance Training (BFRRT) group. Randomization will be executed using an automated, computer-generated sequence with a permuted block design (block size of 2) to ensure a strictly balanced allocation between the treatment arms.

To maintain strict allocation concealment, the randomization sequence will be generated and managed by an independent research coordinator who is not involved in participant recruitment, daily interventions, or outcome evaluations. Individual group assignments will be enclosed in sequentially numbered, opaque, sealed envelopes, which will be opened only after the participant completes all baseline evaluations.

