### Study design and ethical approvals

2.1

This is a single-center, prospective, randomized, parallel-group, open-label clinical trial protocol designed to compare the effects of two cardiopulmonary rehabilitation (CR) protocols—resistance training with versus without blood flow restriction (BFRRT)—in patients with heart failure (HF).

This study protocol is structured and will be reported in accordance with the Standard Protocol Items: Recommendations for Interventional Trials (SPIRIT) guidelines. The study protocol received ethical approval from the Institutional Review Board of the Catholic University of Brasília (UCB) (Brasília, Brazil) under protocol number CAAE 64955022.9.1001.0029.

Written informed consent will be obtained from all participants prior to their formal inclusion in the trial. The investigation will be conducted in strict accordance with the ethical principles outlined in the Declaration of Helsinki (Table 1).

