### Sample size calculation

2.2

The sample size calculation was informed by the data reported by Tanaka et al. [13], who evaluated a BFR-based exercise protocol in patients with HF (New York Heart Association [NYHA] functional class I or II). In their trial, a post-training reduction in brain natriuretic peptide (BNP) of 73 ± 68 pg/mL was observed in the BFR group, compared to a reduction of 15 ± 70 pg/mL in the conventional CR control group [13].

Based on these values, a Cohen's *d* effect size of 0.83 was calculated. Assuming a 1:1 allocation ratio between the experimental arms, a minimum of 24 patients per group is required to achieve a statistical power of 80% with a two-tailed alpha level of 0.05. To account for an anticipated attrition rate of approximately 10%, the final sample size has been established at 26 patients per treatment arm, resulting in a total target recruitment of 52 participants. BNP data from Tanaka et al. were used as the closest available proxy because both biomarkers reflect cardiac wall stress and no directly comparable BFR exercise trial reporting NT-proBNP was available, although this trial will evaluate N-terminal pro-brain natriuretic peptide (NT-proBNP) as its primary biochemical outcome.

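### A fixed, published block size of 2 in a single-centre, open-label trial leaves half the allocations deducible by anyone who knows the preceding one

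*Protocol article*

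**What the plan says.** Section 2.5.3 (Randomization and allocation concealment) of the protocol article states that "participants will be randomly assigned (1:1") by a computer-generated sequence "with a permuted block design (block size of 2) to ensure a strictly balanced allocation between the treatment arms". It describes no stratification, no separate lists by recruiting clinic and no variation in block size.

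The same section makes the concealment claim: "To maintain strict allocation concealment, the randomization sequence will be generated and managed by an independent research coordinator", a person with no part in recruitment, training or outcome assessment. The mechanism is also given: "Individual group assignments will be enclosed in sequentially numbered, opaque, sealed envelopes", "which will be opened only after the participant completes all baseline evaluations".

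Section 2.1 calls the study a "single-center, prospective, randomized, parallel-group, open-label clinical trial protocol". Section 2.2 sets the size, "resulting in a total target recruitment of 52 participants", at 26 per arm.

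**The concern.** Concealment means that whoever decides on the next patient's entry cannot know the arm that patient will get. Envelopes and an outside list-holder protect against someone reading the list. They do not protect against someone working out the next entry from the last one. With a fixed block of 2 that takes no skill, and the block size is in print.

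The protocol leaves room for such knowledge to act:

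- Some exclusions call for judgement (relative contraindications to exercise, severe orthopaedic or cognitive limitation; section 2.4.2).
- Consent comes before randomisation (Table 1), so the order of entry can shift.
- The population mixes HFrEF with HFpEF and NYHA class II with III (section 2.4.1), so who enters which arm matters.
- The analysis of covariance names only age and sex as covariates (section 2.5.21). An imbalance in severity would not reliably be adjusted away.

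At stake is the comparability of the arms, on which the NT-proBNP comparison and the secondary comparisons rest. An objective assay limits measurement bias. It does nothing about who was enrolled.

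**Working it through.** **Inputs.** Block size 2, ratio 1:1 and one sequence (section 2.5.3); single centre, open label (section 2.1); 52 patients, 26 per arm (section 2.2).

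**The plan's own figure.** The sample size enters here only as a count, but it reproduces. The effect size is (73 − 15)/70 = 0.83, and a two-sided 5% t-test with 80% power needs 23.8, so 24 per arm (power 80.4%). The plan raises this to 26 for attrition, so N = 2 × 26 = 52.

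**Determined allocations.** In a fixed block of size 2m whose size is known, the expected share of allocations fixed by the earlier ones in the block is 1/(m + 1).

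| Block size | m | Share determined | Of 52 |
|---|---|---|---|
| 2 | 1 | 1/2 = 50% | 26 |
| 4 | 2 | 1/3 = 33% | 17.3 |
| 6 | 3 | 1/4 = 25% | 13 |

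**Guess rate with blocks of 2.** The first slot of a pair is guessed at 50% and the second at 100%: (0.50 + 1.00)/2 = 75%. With no information it would be 50%.

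**From steering to an arm difference (assumption).** Of the 26 determined slots, 13 are expected in each arm. Suppose patients entered at those slots differ from the rest by +δ SD when one arm is due and −δ SD when the other is due. Each arm mean moves by (13/26) × δ = δ/2, in opposite directions, so the arms differ by δ.

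- All determined slots, both directions, δ = 0.2: difference 0.2 SD.
- One arm only, or half the slots in both directions, δ = 0.2: difference 0.1 SD.
- One arm only and half its slots, δ = 0.2: difference 0.05 SD.

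**Type I error.** For an unadjusted two-sided t-test with 26 per arm, there are 50 degrees of freedom, the critical value is 2.009 and the noncentrality is Δ × √(26/2) = 3.606Δ.

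| Arm difference Δ (SD) | Noncentrality | Type I error |
|---|---|---|
| 0 | 0 | 5.0% |
| 0.05 | 0.180 | 5.4% |
| 0.1 | 0.361 | 6.4% |
| 0.2 | 0.721 | 10.9% |

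**The alternative.** I simulated a random mix of blocks of 4 and 6, cut at 52, for an observer who sees every earlier allocation and knows that the sizes are 4 and 6 but not their order. Fully determined allocations fall from 50% to about 6% (about 3 of 52), and the guess rate falls from 75% to 69%. The final arm difference never exceeds 2. At 27 v 25 the efficiency loss is 1 − 4 × 27 × 25/52² = 1 − 2700/2704 = 0.15%.

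**The case against.** The strongest defence is that the protocol does more than many: an outside sequence-holder, proper envelopes, and opening only after that patient's baseline tests. Several stronger readings of the flaw are tempting, and the document does not support them.

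- **That concealment is absent altogether.** It is not. The first allocation of each pair, 26 of 52, remains unpredictable.
- **That staff will know the preceding assignment.** The protocol does not say who opens the envelopes or who learns the result. Patients come from several clinics and hospitals (section 2.3), so recruiters need not be trainers. Section 2.5.4 gives both arms the same low-load training for two weeks, and arm-specific training starts only in week 4 (section 2.5.5). This is partial protection at best. Table 1 places randomisation at baseline, before training begins, and labels the adaptation row as applying to CRT only, which leaves the common phase unclear. No rule restricts knowledge of opened assignments, and recruiting from several clinics does not help when they share one sequence.
- **That type I error is 11% or more.** A difference of 0.2 SD needs steering at every determined slot in both directions, and 0.3 SD (18.6%) needs more still. The shift must also fall on the change in NT-proBNP, which is hard to foresee at enrolment.
- **That no analysis could help, or that subjective outcomes are specially exposed.** Adjustment can reduce bias that runs through measured baseline variables. Selection bias does not depend on how subjective an outcome is.

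What stands is that predictability follows from the stated rule, and no other section repairs it. The gain in guess rate from larger blocks is also modest, which is a fair limit on the remedy.

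**Conclusion.** The point holds for half the allocations. With the stated rule, 26 of 52 assignments are certain to anyone who knows the preceding one and its place in the pair, so the claimed strict concealment is not secured for them. That part is arithmetic and rests on no assumption about conduct.

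The consequence is possible bias, not shown bias. It requires that enrolling staff learn earlier assignments, which the protocol neither states nor prevents, and that they act on them, knowingly or not. A plausible range for the type I error is about 5.4% to 10.9%, with the upper end close to a worst case for δ = 0.2. These figures are for an unadjusted t-test on all 52 patients; the planned adjustment for age and sex would not reliably remove the bias. The wish for strict balance does not justify blocks of 2, since larger blocks give almost the same balance.

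**What to change.** In section 2.5.3, replace the block of 2 with randomly varying blocks, for example 4 and 6, generated by the same independent coordinator. Withhold the sizes from recruiting, assessing and training staff, and from public text until enrolment ends. The main gain is far fewer fully determined allocations, and it depends on the sizes staying hidden.

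It is unclear whether enrolment has begun: section 2.1 puts consent in the future, the ethical compliance statement in the past. If it has, regenerate all unopened envelopes, including the second of any open pair, and report the date of the change.

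The cost is a new list, new envelopes and one or two sentences of protocol text. The sample size does not change. The final imbalance is at most 2 patients at 52 (0.15% efficiency loss). If the change falls in mid-pair, it could reach 4, that is 1 from the open pair plus 3 from a cut block of 6: 28 v 24, a loss of 1 − 4 × 28 × 24/52² = 0.59%.

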#### Exercise intervention protocol

2.5.4

The structured cardiopulmonary rehabilitation (CR) program will span a 16-week period, with sessions conducted twice weekly, each lasting approximately 30 min. The initial 2 weeks of the program will serve as a standardized adaptation phase, during which all participants across both experimental arms will perform low-load conventional resistance training.

In the third week, a one-repetition maximum (1RM) test and retest procedure will be executed to establish baseline dynamic muscular strength for training load prescription. To minimize the risk of cardiovascular adverse events and avoid maximal intra-thoracic pressure or prolonged Valsalva maneuvers in this clinical population, maximum muscular strength will be indirectly estimated via submaximal testing using the Brzycki prediction equation [14]:$$1\text{RM}=\frac{\text{Load}}{\left(1.0278\;–\;\left(0.0278\;\times \;\text{Reps}\right)\right)}$$Where Load represents the submaximal weight lifted (expressed in kilograms) and Reps denotes the number of repetitions completed until volitional fatigue, not exceeding 10 repetitions. This submaximal 1RM estimation protocol will be performed for all selected exercises at baseline to calculate the exact relative percentages for training prescription, and it will be repeated during the final week of the 16-week intervention to evaluate muscular strength progression as a secondary outcome.

#### Training cycles and periodization progression

2.5.5

The structured intervention within the allocated groups (CRT or BFRRT) will commence in the fourth week of the program. The macrocycle will be partitioned into two distinct 6-week training blocks. To ensure appropriate progressive overload, a submaximal 1RM reassessment will be conducted at the end of the first 6-week block to recalibrate relative training loads. A final submaximal 1RM evaluation will be executed during the sixteenth week to analyze long-term muscular strength progression.

#### Session structure and exercise selection

2.5.6

Each training session will initiate with a 5-min quiet rest period in the seated position for baseline hemodynamics and blood pressure monitoring. Participants will then perform a 5-min warm-up on a motorized treadmill at a self-selected comfortable pace, followed immediately by the resistance training circuit.

The circuit will comprise the following five exercises targeted at major muscle groups:

Horizontal leg press; Seated chest press (bench press machine); Seated lat pulldown; Leg curl; Standing calf raises (plantar flexion). Following session completion, a 5-min passive recovery period will be observed, followed by final blood pressure and heart rate measurements.

#### Group-specific interventions and loading conditions

2.5.7

To isolate the therapeutic effect of vascular occlusion, the structural variables—including the number of sets, repetitions, and rest intervals—will be identical between groups, whereas the external training intensities differ by design: Conventional Resistance Training (CRT) Group: Participants will perform 3 sets of 15 repetitions at a moderate-to-high intensity of 60–80% of 1RM, maintaining a 45-s passive rest interval between sets. Blood Flow Restriction Resistance Training (BFRRT) Group: Participants will execute 3 sets of 15 repetitions at a low external intensity of 20–30% of 1RM, maintaining a 45-s passive rest interval. For this group, blood flow restriction will be applied continuously throughout both the active exercise bouts and the brief inter-set rest periods, and it will be deflated immediately upon completion of the third set of each exercise.

#### Vascular occlusion pressure calibration

2.5.8

For the BFRRT group, the total arterial occlusion pressure (AOP) will be determined in the fourth week and reassessed alongside the submaximal 1RM tests to account for anatomical and localized adaptations. Measurements will be performed by a trained investigator using a portable vascular Doppler probe (DV 610 B, Medmega, Brazil) to detect the cessation of the auscultatory pulse.

Vascular occlusion will be applied using a clinical blood flow restriction system equipped with a removable aneroid manometer and high-resistance velcro cuffs (Avanutri, Rio de Janeiro, Brazil). To standardize application, the baseline AOP measurement will be performed while the patient is positioned in a relaxed, standing orthopedic posture (anatomical position). The restriction pressure during the sessions will be dynamically calibrated and monitored in real time via the integrated aneroid gauge, set at a standardized, individualized target of 50% of the total AOP for both the upper and lower limbs. The cuffs will remain continuously inflated throughout the specific exercise execution and its corresponding 45-s inter-set rest intervals; however, the cuffs will be completely deflated immediately upon completion of the final set of each exercise and will remain deflated during transitions between different exercise stations to ensure patient safety and comfort.

#### Procedures

2.5.9

During the first two weeks, participants will undergo comprehensive baseline clinical evaluations. Body composition will be assessed via dual-energy X-ray absorptiometry (DXA) as the primary laboratory standard; additionally, skinfold thickness measurements will be collected as a methodological safeguard and field-based backup to ensure data continuity throughout the long-term trial. Vascular health, cardiorespiratory fitness, and functional performance will be evaluated using the ankle-brachial index, cardiopulmonary exercise testing (ergospirometry), the 6-min walk test, and the 30-s sit-to-stand test.

Muscle strength will be assessed through knee-joint isokinetic dynamometry and handgrip strength. Furthermore, biochemical analyses will be performed to measure blood-borne biomarkers: hemostasis markers (D-dimer, fibrinogen, and activated partial thromboplastin time—aPTT) will be monitored as a clinical safety protocol, alongside systemic inflammatory markers (C-reactive protein) and tissue-specific microRNAs (vascular, skeletal muscle, and cardiac-specific).

Cardiac structure and function will be analyzed via resting transthoracic echocardiography, while health-related quality of life will be measured using the Minnesota Living with Heart Failure Questionnaire.

#### Dual-energy X-ray absorptiometry

2.5.10

Body composition will be assessed via whole-body Dual-Energy X-ray Absorptiometry (DXA), using the DPX-IQ model (Lunar, Madison, USA), which will be properly calibrated daily according to the manufacturer's operational recommendations. Prior to the scanning procedure, participants will be instructed to remove all metallic accessories, jewelry, and clothing components containing metal to prevent X-ray attenuation artifacts.

During the diagnostic scan, participants will remain completely immobile in the supine position on the central axis of the equipment table. Their arms will be positioned minimally away from the trunk with palms facing downward, and their feet will be secured apart to standardize tracking boundaries. For safety compliance, individuals fitted with permanent cardiac pacemakers or Implantable Cardioverter Defibrillators (ICDs) will be strictly excluded from performing this specific imaging test.

#### Skinfold thicknesses

2.5.11

To evaluate subcutaneous body fat distribution, skinfold thicknesses will be collected across the following nine standardized anatomical sites: biceps, triceps, subscapular, pectoral, midaxillary, suprailiac, abdominal, medial thigh, and calf. All anthropometric markings and localized tissue caliper placements will be executed in strict accordance with the morphological procedures outlined by the American College of Sports Medicine (ACSM) Guidelines for Exercise Testing and Prescription, 11th Edition [15].

These manual measurements will be performed unilaterally on the right side of the body by a single, experienced investigator to eliminate inter-rater variability. The evaluator will maintain a verified test-retest reliability coefficient greater than 0.95 for each separate anatomical site and a maximum technical error of measurement (TEM) restricted to ±1.0 mm, utilizing a calibrated Lange skinfold caliper. All physical measurements will be captured using a rotational tracking order, repeated three separate times per site, and logged by an independent data recorder. The median value of the three consecutive trials for each anatomical landmark will be adopted as the formal baseline reference.

Total body density will be calculated from the cumulative skinfold thickness arrays utilizing generalized predictive equations validated for adult and older clinical cohorts. The Jackson and Pollock 7-skinfold mathematical protocol will be deployed for both male and female configurations; this specific model is selected because it actively incorporates chronological age as a corrective biological variable, which is critical for accurate body composition tracking within the targeted 40–70 age spectrum [15]. Subsequently, the estimated body density metrics will be converted to isolate the final relative body fat percentage using the standard Siri formulation [16].

